##### EBRB-targeted components

In the Mindfulness VIP training, several exercises aimed at (determinants of) EBRB will be integrated in the program as well, such as: "walking meditation", "mindful eating" and "shopping for groceries mindfully".

##### E-coaching

Mindfulness trainers will perform e-coaching to continue implementing the mindfulness principles learnt in the training. In the seventh session of the training, participants will be invited to formulate goals and think of ways to achieve them in the format of a Personal Energy Plan (PEP) as homework. Participants will be asked to return the PEP by email to the trainer. This PEP functions as the basis for the coaching; participants will monitor their personal goals and reflect on their progress in the PEP journal. To maximize the effects of the goal setting, the goals should correspond to personal values and needs [41]. To obtain a maximum of effect, the goal setting in the PEP plan will be preceded by a personal value exercise in the training. Attaining goals that match personal values not only contributes to attaining the goals, but also to subjective well-being [42]. Therefore, this contributes also to work engagement as this is a positive affective-cognitive state just like well-being, only work-related [34].

##### Supporting elements

There will be three supporting elements in this intervention: providing fruit at work, providing routes for lunch walking, and stimulation (by the mindfulness trainer) to find a buddy for several activities. This buddy can be a facilitator to attend to mindfulness sessions, help with the homework exercises for the mindfulness training, accompany the subject on lunch walking, join in exercising, share commuting to work by bike, or to talk about work and reflect on the learning process. During the mindfulness sessions, homework exercises will be discussed with a buddy.

#### Step 5 Development of a Plan for Implementation

Two additional participatory focus groups were convened to design a plan for implementation. Participants included the intended implementers as well as the recipients of the intervention. Both groups discussed the possibilities for success and potential challenges of the implementation of the intervention. The outcomes from these focus group sessions were embedded in the instruction of the trainers. It was decided to use a down-to-earth approach with participants in the intervention and to use clear language with straightforward formulated instructions and explanations. Such an approach would avoid the risk of deterring intended participants from the intervention.

#### Step 6: Evaluation

The evaluation of the effectiveness will be presented in the next section.

### Phase II: Evaluation of the Intervention

#### Study Design

The effectiveness of the Mindfulness VIP program will be measured using a RCT. Participants who have given informed consent were measured at baseline (T0), and will be measured at 6 months (T1) and 12 months (T2). The study design and procedures have been approved by the Medical Ethics Committee of the VU University Medical Center.

#### Population

The study population included employees of two Dutch research institutes in the governmental sector. Most workers are highly educated (most have completed higher vocational education or university), who perform sedentary work. All employees at both institutes were invited to participate in this study. Exclusion criteria were being on sick leave for more than four weeks or being pregnant at the time of recruitment.

#### Randomisation and Blinding

Randomisation was performed at individual level, directly after the baseline measurement (T0), using a computer-generated randomisation sequence in SPSS by an independent researcher. As a result of the nature of the intervention, blinding of the participants and the trainers was not possible.

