#### Step 1: Needs Assessment

For this first step, the needs of the target population were assessed by:

1) exploring the work engagement and selecting EBRB of the target population: highly educated workers of two public research institutes

2) exploring the key resources and determinants of work engagement and EBRB of the target population.

1) A literature search was performed, face-to-face interviews were held, and a brief questionnaire was distributed among workers to gain insight into the work engagement and EBRB of the target population.

The mean score for work engagement for Dutch workers is 3.82, measured in a representative sample of Dutch workers using the Utrecht Work Engagement Scale (UWES), on a scale from zero to six, where zero is the most negative and six the most positive [7]. No specific data on work engagement are known for the governmental sector, scientific professions or higher educational levels.

Dutch workers, on average, spend about seven hours total per day sitting--one third of this at work [23]. Sedentary behaviour at work can not be compensated by increased physical activity in leisure time. Furthermore, workers in the governmental sector (to which the target group belongs) are amongst the top five sectors in which workers spent significantly more time sitting at work and in total during the day than the average Dutch worker [23].

Face-to-face interviews were held with six key figures in one study research institute to gain insight into the characteristics of work engagement and EBRB of the target population. Managers, Human Resource Management officers, and staff assistants characterized the target population as highly motivated and involved workers, who spent a lot of time on cognitive activities. The key figures stated that mental well-being was more of a priority for this population than EBRB, and they believed there were more mental problems than physical ones in this group.

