#### Recruitment

The usual and available communication channels of the participating organisations were used to recruit participants. These channels included intranet, internet, a personnel magazine, posters on bulletin boards and digital newsletters. Efforts were made to create support from supervisors and directors. Workers were also invited by email. In one of the participating organisations, an additional mailing (hard copy) was distributed.

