#### Effect Evaluation

The effectiveness of the intervention will be analysed using a regression analysis (analysis of covariance) with the outcome measure at follow-up (T1: 6 months and T2: 12 months) as the dependent variable and adjusting for the baseline levels of the outcome measure. In addition, a Generalised Estimated Equations (GEE) analysis will be performed for the long-term effects (baseline to 12 months). All statistical analyses will be performed according to the intention-to-treat principle. For all analyses a two-tailed significance level of < 0.05 will be considered statistically significant. All analyses will be performed with SPSS 16.0 (SPSS Inc. Chicago, Illinois, USA).

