### Strengths and Limitations

The first strength of the Mindful VIP study is targeting two threats to worker's health in the Western society: mental health problems and overweight as a result of a disturbed energy balance. A second strength of this study is that by developing the intervention in a systematic way, based on the IM protocol, the intervention is theory-based and the target population was involved in the development as well. As a result, the intervention is likely to be adequate to meet the needs of the target population, hopefully resulting in good compliance. Discussing the constraints of the implementation of the program and compliance with the target population decreases the likelihood of barriers in adoption of the program. Furthermore, the effectiveness will be evaluated in a two-armed RCT with two follow up measurements up to one year. Another strength of the study is that anthropometric measurements are conducted objectively, and physical activity and sedentary behaviour data are collected using a combination of subjective and objective methods.

This study also has limitations. As the intervention was developed for and by the target population, it is possible that this intervention is only suitable for the present study population. This means that the external validity might be limited. However, we feel that the intervention and study's results might be applicable to many other highly educated office workers as well. The two research institutes are comparable to the extent that they both conduct policy-based research, and mainly include office workers who perform mentally demanding work.

Another limitation of the study design is that blinding participants is not possible. On the one hand, the likelihood of a spill-over effect (i.e. contamination) is expected to be negligible, because the training and e-coaching only is accessible for those in the intervention group. On the other hand, all workers, for example, might take fruit when informed by colleagues from the intervention group. When evaluating the effects, this should be considered.

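### Institute is missing from the stated randomisation, effect model and baseline table: no bias follows, but adding it as a covariate removes avoidable chance error at almost no cost

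*Protocol article*

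**What the plan says.** Under Population: "The study population included employees of two Dutch research institutes in the governmental sector". The Discussion refers to the larger of the two, so the workforces are unequal in size. How the 257 randomised participants divide between the institutes is not given.

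Under Randomisation and Blinding: "Randomisation was performed at individual level, directly after the baseline measurement (T0), using a computer-generated randomisation sequence in SPSS". No stratification factor is described.

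Under Effect Evaluation, the follow-up outcome at 6 and 12 months enters "as the dependent variable and adjusting for the baseline levels of the outcome measure". No institute term is named there, and no covariates are listed for the GEE model. The Economic Evaluation section states no covariate adjustment for the cost comparison. Its inputs include sickness absence from company records and productivity losses valued at participants' salaries.

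Table 5 lists demographics, engagement, behaviours and weight status by arm, but not institute. The Discussion concludes from these characteristics that randomisation succeeded.

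**The concern.** Institute is the one structural factor in this trial and is known for every participant. Two employers may differ in how engagement, absence and pay develop over a year, and the baseline score need not capture all of that. If they do differ, and the arms happen to hold different shares of each institute, part of the between-arm difference reflects institute rather than the programme. A reader cannot see whether such an imbalance occurred, because the table that supports the statement on randomisation omits it.

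What is at stake is precision and transparency. On the primary endpoint the effect is small. The case for the covariate is somewhat stronger for costs, since absence records and salaries belong to the employer, but the article gives no figures from which to size it.

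**Working it through.** **Inputs from the article.** Arms of 129 and 128 (Baseline Characteristics). Reference mean 3.82 with SD 1.1, a 10% increase as target (0.382), two-sided alpha 5%, power 90%, 25% loss to follow-up, revised SD 0.83 (Sample Size Calculation).

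**Assumptions, not in the article.** Share of participants in the larger institute: 50% to 90%. Difference D between institutes at follow-up: 0.2 to 0.5 UWES points.

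**1. The plan's own figure.** n per group = 2 × [1.1 × (1.960 + 1.282) / 0.382]² = 174.3, so 175. Then 175 / 0.75 = 233.3, so 234 per group and 468 in total. This reproduces the initial calculation and confirms 0.382 as the target difference used there.

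**2. Chance imbalance without stratification.** SD of the between-arm difference in institute share = √[p(1 − p)(1/129 + 1/128)].
- p = 0.5: 0.0624; × 1.96 = 12.2 percentage points.
- p = 0.8: 0.0499; × 1.96 = 9.8 percentage points.

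**3. What that does to the estimate.** The shift is the imbalance times D. Its 95% range with D = 0.382 is ±0.047 at 50:50 and ±0.028 at 90:10. With D = 0.5 at 50:50 it is ±0.061. The standard error of the unadjusted effect is 0.83 × √(1/129 + 1/128) = 0.104. The SD of 0.83 already contains any spread between institutes, so the usual confidence interval already allows for this shift.

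**4. Bias and type I error.** Unstratified 1:1 allocation was simulated with 194 analysed (97 per arm; 129 × 0.75 = 96.75), total SD held at 0.83, no true effect and no institute term. Larger-institute shares were 50%, 70% and 90%, and D was 0.2, 0.382 and 0.5. The mean estimate lay between −0.004 and +0.001. The rejection rate lay between 0.046 and 0.056, with a simulation standard error of √(0.05 × 0.95 / 8000) = 0.0024. There is no sign of bias or of meaningful inflation.

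**5. Gain from the institute term.** With a true effect of 0.382, simulated power was 0.88 to 0.90 without the term and 0.89 to 0.91 with it. The largest gain was 2.7 points, at 50:50 and D = 0.5. A direct check of that case:
- Without the term: 0.382 / (0.83 × √(2/97)) = 3.205; power = Φ(3.205 − 1.960) = 0.893.
- With the term: residual SD = √(0.83² − 0.25 × 0.5²) = 0.791; 0.382 / (0.791 × √(2/97)) = 3.361; power = Φ(1.401) = 0.919.
- Gain: 2.6 points.

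With D = 0.2 at 50:50 the same formula gives 0.898, a gain of 0.4 points. These runs contain no baseline covariate, because the article gives no baseline-to-follow-up correlation. Baseline adjustment would remove some of the institute difference as well.

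**6. What a per-institute estimate could show.** With an assumed 80:20 split and 25% loss, the smaller institute keeps 257 × 0.2 × 0.75 = 38.6 participants, about 19.3 per arm. The 95% half-width is 1.96 × 0.83 × √(2/19.3) = 0.52, which is wider than the target effect of 0.382.

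**The case against.** The strongest reply is that nothing in the two sections is wrong. Individual randomisation makes institute independent of arm. This is also a condensed article: a full protocol or analysis plan may name a stratification factor or further covariates, and the phrase "adjusting for the baseline levels of the outcome measure" does not exclude them. All of that stands, and it is why the point is an improvement to the stated model and not an error in it.

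A reader might still infer that a difference between institutes passes into the treatment effect as hidden bias. The documents do not support this. A chance imbalance is random error, and the standard error already counts it (steps 3 and 4). Multiplying an outer-limit imbalance by a large assumed institute difference, and setting the product against the target effect, would describe an extreme and not an expected distortion.

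A reader might also cite two differences between the institutes: "In one of the participating organisations, an additional mailing (hard copy) was distributed" and "Face-to-face interviews were held with six key figures in one study research institute". Both precede randomisation, so neither can confound the arms. The interviews belong to intervention development, where a questionnaire and focus groups were used as well.

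Nor does the article claim equal effects in both workplaces. It writes "The two research institutes are comparable to the extent that they both conduct policy-based research" and words the wider applicability of its results cautiously.

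These replies leave untouched that the stated model names no term for a known structural factor, and that Table 5 does not let a reader check it.

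**Conclusion.** The point holds as a minor improvement that is almost free. The stated plan yields an unbiased effect with type I error near 5%. It accepts avoidable random error from an institute imbalance whose 95% range is about ±12 percentage points at a 50:50 split and ±10 at 80:20. Under assumed institute differences of 0.2 to 0.5 UWES points, adjustment would gain roughly 0 to 3 points of power. If the institutes do not differ at follow-up given baseline, the gain is nil. The split of participants, the institute difference and any effect on the cost comparison cannot be established from the article.

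**What to change.** - Before follow-up data are analysed, state whether the sequence was stratified by institute, and name institute as a fixed binary covariate in the analysis of covariance at 6 and 12 months and in the GEE model.
- Use the same term in the cost comparisons, where employer-specific absence records and salaries enter.
- Add institute by arm to Table 5 as a descriptive row.
- If effects per institute are shown, give them with confidence intervals and label them descriptive. Given the width in step 6, they should not be used to claim that the effect is equal in both workplaces.

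The cost is one degree of freedom per model and one table row, using information already held. A fuller protocol or analysis plan that already contains these items would only need to be cited.

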#### Recruitment

The usual and available communication channels of the participating organisations were used to recruit participants. These channels included intranet, internet, a personnel magazine, posters on bulletin boards and digital newsletters. Efforts were made to create support from supervisors and directors. Workers were also invited by email. In one of the participating organisations, an additional mailing (hard copy) was distributed.

#### Procedure

Consenting participants were randomised to the intervention or control group after the baseline measurement. The control group as well as the intervention will be asked to complete the two follow-up measurements after 6 (T1) and after 12 months (T2).

### Primary Outcome Measurements

The primary endpoint of this study will be work engagement as measured by the Utrecht Work Engagement Scale (UWES). The UWES consists of three aspects: vigor (6 items), dedication (5 items), and absorption (6 items) [7]. The three aspects combined result in an overall work engagement score. Varying from 0 to 6; a higher UWES score indicates a higher work engagement.

### Secondary Outcome Measurements

#### Energy Balance-Related Behaviours

Physical activity was assessed by the Short Questionnaire to Assess Health Enhancing Physical Activity (SQUASH) [43]. It measures duration, frequency and intensity of work transportation, household activities, leisure activities and work activities. In accordance with the second program objective, the weekly level of physical activity of vigorous intensity in leisure time was assessed by an item documenting how often these activities were performed for at least 20 minutes.

Questions related to sedentary behaviour at work include the time spent (in minutes per day) on: 1) computer use, 2) reading, 3) meetings, 4) calling and 5) other activities. Additionally, physical activity and sedentary behaviour were measured objectively using a single waist-worn Actigraph Computer Science and Applications accelerometer. This accelerometer collected data on activity, step count and three axes (with an epoch period of 60 seconds over seven consecutive days) at baseline and at follow-up measurements among a randomly chosen subsample of 100 participants. The same 100 participants were asked to wear the same accelerometer at the follow-up measurements. To interpret the data obtained by the accelerometer adequately, participants were asked to keep a logbook of their physical activities and sedentary behaviour during the seven days of wearing the meter.

Dietary behaviour was assessed by focussing on fruit and vegetable intake using the Short Fruit and Vegetable Questionnaire [44]. The questionnaire consists of 10 questions: six for fruit consumption and four for vegetable consumption.

#### Mental and Physical Health-related Outcome Measures

Mental health, vitality and general health perceptions were all measured by the corresponding items within the RAND-36 [45]. For the Mental Health Inventory from the RAND-36, participants were asked to indicate on a six-point scale for five items how often they felt anxious, depressed, calm, sad and happy during the past four weeks. For vitality, participants were asked to indicate on a six-point scale how often they felt full of life, worn out, tired and full of energy over the past four weeks. For general health perceptions, participants were asked to indicate on five items how they perceive their health (on a five-point scale from excellent to bad) and to indicate on four propositions to what extent they agree (using a five-point scale).

##### Mindfulness

The level of mindfulness was measured using the Mindful Attention Awareness Scale (MAAS) [31]. This 15-item scale measures the frequency of everyday mindfulness experiences on a six-point scale.

##### BMI and waist circumference

All anthropometric measurements were performed by trained research assistants. Overweight and obesity are commonly measured by the body mass index (BMI). BMI is calculated by dividing body weight in kilograms by the square of the body height in meters. Height was measured to the nearest 0.1 cm without shoes. Weight was measured to the nearest 0.5 kg in participants wearing indoor clothing and no shoes, after emptying their pockets. Waist circumference was measured as midway between the lower rib margin and the iliac crest to the nearest 0.1 cm [46]. Participants were measured standing up, breathing out gently, in indoor clothing, after emptying their pockets. All measurements are repeated to increase reliability.

##### Need for recovery

The 11-item 'need for recovery scale' from the Dutch version of the Questionnaire on the Experience and Evaluation of Work (Dutch abbreviation VBBA) were used [47].

##### Measures of determinants of behaviour

Based on models of behaviour, questions were asked on perceived behavioural control, intention and perceived barriers (lack of time) for physical activity and dietary behaviours.

##### Prognostic factor

The need for cognition (prognostic factor) was assessed using the short version of the Need for Cognition Scale [48]. This scale consists of 18 items on which subjects have to indicate on a five-point scale to what extent the item is characteristic of them. Items assess engagement in and enjoyment of thinking, learning and intellectual cognitive activities.

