##### Strategies

The program's self-regulation strategy was mindfulness training. Mindfulness can be described as "an open, undivided observation of what is occurring both internally and externally" [31] (p. 823). Hypothetically, mindfulness training best fits the study's target group, as it is likely to attract individuals who have a high need for cognition because they pay attention to relevant arguments [32].

Mindfulness training has been shown to be effective in improving aspects of both mental and physical health [33]. Although evidence of mindfulness training strategies to improve work engagement is lacking, evidence does exist that it can improve subjective well-being; this is relevant because work engagement can be seen as subjective well-being at work [34]. Proven effective activities to improve subjective well-being can be divided into three categories: behavioural, cognitive and motivational. A cognitive activity that can improve subjective well-being is mindfulness [34]. In the Mindful VIP study several activities were integrated in the program (see Step 4 for details). Furthermore, the effectiveness of mindfulness training to increase physical activity and to stimulate body weight reduction has been demonstrated in small scale interventions [32,35].

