Baseline findings confirmed the findings and assumptions resulting from the needs assessment. Consistent with findings in the needs assessment and with findings in the Dutch population [7], the mean score for work engagement at baseline was average (according to scores defined by Schaufeli & Bakker [7]). Therefore, aiming at an increase in work engagement is considered feasible, as well as relevant. An increase in vigorous physical activity in leisure time, and a decrease in sedentary behaviour at work, are also feasible and relevant. Especially relevant would be to decrease the number of people not engaging in vigorous physical activity at all. The mean number of minutes per week engaging in vigorous physical activity and its non-normal distribution is comparable to a certain degree to findings in previous research [43] (mean = 70, sd = 168). Workers involved in the needs assessment indicated that they thought body weight was less important than mental health and well-being. The percentage of overweight and obese workers in the study population, 29% and 9%, respectively, was consistent with the Dutch working population, which is 31% overweight and 6% obese [58]. This is remarkable, however, since according to the same study, the prevalence of overweight and obesity among Dutch workers with scientific professions is significantly lower than the Dutch overall prevalence, namely 25.7% and 4.2%, respectively. Not all workers at the research institutes and included in this study perform scientific work, which may explain this discrepancy.

When making the choice for mindfulness training as a strategy of self-regulation, the need for cognition was assumed to be high. This was indeed the case, as the study population's need for cognition was relatively high (3.67-3.75 on a scale from 1 to 5).

Because the baseline characteristics were congruent with the findings in the needs assessment and the expectations on which the intervention was developed, we concluded that the systematic development based on the IM protocol produced a potentially appropriate intervention program, meeting the needs of this target population.

Furthermore, the baseline characteristics show that the intervention and control group did not differ significantly. Therefore, we concluded that randomization was successful, although for vigorous physical activity the groups did differ at baseline and this should be kept in mind when evaluating the effects.

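### Need for cognition is named as the trial's one prognostic factor, yet the stated effect models adjust at most for the baseline outcome; adding it for work engagement is a minor gain in precision

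*Protocol article*

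**What the plan says.** Under Prognostic factor, the article states that "The need for cognition (prognostic factor) was assessed using the short version of the Need for Cognition Scale". The scale has 18 items. Table 5 gives the variable its own block under the same label, and no other variable is labelled in this way. The means are 3.67 (SD 0.51) in the intervention group (n = 129) and 3.75 (SD 0.59) in the control group (n = 128). According to Randomisation and Blinding and Baseline Characteristics, allocation followed the baseline measurement, so this is a pre-randomisation variable.

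Under Effect Evaluation, the ANCOVA takes the outcome at 6 months (T1) and 12 months (T2) "as the dependent variable and adjusting for the baseline levels of the outcome measure". No other covariate is named. The same paragraph adds a GEE analysis from baseline to 12 months and gives no covariates for it.

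Need for cognition appears in two other roles. Under Strategies it supports the choice of mindfulness training, because "it is likely to attract individuals who have a high need for cognition because they pay attention to relevant arguments". In the Discussion its baseline level is used to confirm that this expectation was met. Neither section links it numerically to work engagement, the primary endpoint.

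**The concern.** The two sections do not fit together well. One declares a variable prognostic. The other says what the effect model adjusts for and does not include it. Either the label is loose or the list of covariates is incomplete.

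The reason to resolve this does not depend on any baseline imbalance. In a linear model, a covariate that predicts the outcome beyond its baseline value reduces the residual variance and so narrows the interval for the treatment effect, even when the arms are balanced. The data are already collected.

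There is also a prespecification aspect. If the role of the variable is left open until results are seen, the adjusted and unadjusted models both remain available and the choice between them can be questioned.

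**Working it through.** **The plan's own figure.** The article gives no figure for the value of need for cognition as a covariate. Its first sample size was calculated without any covariate and reproduces: difference 10% of 3.82 = 0.382, SD 1.1, 90% power, two-sided 5%, so n = 2 × (1.1 × (1.960 + 1.282) / 0.382)² = 174.3, rounded up to 175 per group.

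**Baseline difference (Table 5).**
- Pooled SD = √((128 × 0.51² + 127 × 0.59²) / 255) = 0.551.
- Standardised difference d = (3.67 − 3.75) / 0.551 = −0.145.
- Test statistic = −0.08 / √(0.51²/129 + 0.59²/128) = −1.16, p about 0.25. This is an ordinary chance difference.

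**Gain in precision.** Let p be the partial correlation of need for cognition with follow-up UWES, given baseline UWES and group. Let r be the correlation of baseline with follow-up UWES. The documents give neither, so both are assumptions. Adding the covariate multiplies the residual SD by √(1 − p²).

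The cost is the share of the group contrast that the new covariate absorbs. With equal arms, the squared correlation of group with need for cognition is d² / (d² + 4) = 0.0210 / 4.0210 = 0.0052. The variance of the estimate is therefore inflated by 1 / (1 − 0.0052) = 1.0053.

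| p | √(1 − p²) | SE change before cost | SE change after cost, √((1 − p²) × 1.0053) |
|---|---|---|---|
| 0 | 1.000 | 0% | +0.3% |
| 0.1 | 0.995 | −0.5% | −0.2% |
| 0.2 | 0.980 | −2.0% | −1.8% |
| 0.3 | 0.954 | −4.6% | −4.4% |

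**How large p might be.** Suppose need for cognition has the same simple correlation c with baseline and follow-up UWES. Then p = (c − rc) / √((1 − r²)(1 − c²)).
- c = 0.1, r = 0.7: p = 0.03 / √(0.51 × 0.99) = 0.04.
- c = 0.4, r = 0.5: p = 0.20 / √(0.75 × 0.84) = 0.25.

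So a range of 0.1 to 0.4 for c, with r from 0.5 to 0.7, gives p of only 0.04 to 0.25. Baseline UWES already carries much of what need for cognition could add.

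**What this means for power.** Take the article's revised SD of 0.83, a difference of 0.382 and its revised 89 per group as printed. The residual SD is 0.83 × √(1 − r²) × √(1 − p²), and power is Φ(0.382 / (residual SD × √(2/89)) − 1.960). For p = 0.1, 0.2 and 0.3:
- r = 0.5: power moves from 94.4% to 94.6%, 95.1% and 96.1%.
- r = 0.7: power moves from 99.0% to 99.1%, 99.2% and 99.5%.

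**Shift in the estimate.** The chance difference in need for cognition moves the estimate by p × √(1 − r²) × d × SD of UWES. The pooled baseline SD of UWES is √((128 × 0.81² + 127 × 0.91²) / 255) = 0.861.
- p = 0.1, r = 0.7: 0.1 × 0.714 × 0.145 × 0.861 = 0.009 points.
- p = 0.3, r = 0.6: 0.3 × 0.800 × 0.145 × 0.861 = 0.030 points.

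That is about 2% to 8% of the planned difference of 0.382.

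**The case against.** The strongest objection is that this is an omission from a condensed article, not an error. The Effect Evaluation paragraph is short, does not exclude further covariates, and a fuller list may stand in an analysis plan that is not shown. The article also never says that need for cognition was collected for adjustment. Its rationale is suitability for the training, which fits effect modification at least as well as prognosis, and the Discussion does use the variable for that purpose. Finally, no correlation with UWES is reported, so any gain is assumed.

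Most of this stands and limits the point. What remains is that the article does state what its ANCOVA adjusts for and separately calls another variable prognostic, so a concrete improvement to the stated model is available at almost no cost.

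Several stronger readings are tempting and are not supported:
- *Precision is being thrown away.* This would need a non-trivial partial correlation, and the documents give none. At zero nothing is gained.
- *The effect estimate is biased, or the imbalance must be corrected.* In a randomised comparison, leaving the covariate out causes no bias and no type I error problem, and the arm difference is unremarkable.
- *The variable goes unused.* It is described by arm and compared at baseline, and it is used to judge the fit of the training.
- *ANCOVA is the only effect model.* The article also says that "a Generalised Estimated Equations (GEE) analysis will be performed for the long-term effects (baseline to 12 months").
- *Every outcome should be adjusted for it.* Nothing links need for cognition to BMI, fruit intake or sitting time.

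**Conclusion.** The point holds as a minor one about efficiency and prespecification. Need for cognition is the one named prognostic factor and is measured before randomisation, while the only covariate stated for any effect model is the baseline outcome.

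For the primary outcome, the expected benefit is a reduction in standard error of 0% to about 4.6%, for an assumed partial correlation of 0 to 0.3. At 0.1 or below there is essentially no net gain once the cost of the extra term is counted. The estimate would move by about 0.01 to 0.03 UWES points under partial correlations of 0.1 to 0.3. The main conclusion of the trial is unlikely to turn on this.

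The size rests entirely on assumed correlations, and the figures use the arm difference in the full randomised sample, which may differ among those followed up.

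A reader might infer from the rationale under Strategies that an interaction analysis is required. The documents do not support that: the trial was sized for a main effect, and a group-by-need-for-cognition term could only be optional and exploratory.

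**What to change.** In Effect Evaluation, for work engagement (UWES) only, state the model as follow-up UWES on group, baseline UWES and baseline need for cognition as a continuous covariate, in the ANCOVA at T1 and T2. Include the same covariate in the GEE. Report the model without need for cognition as a sensitivity analysis.

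Date this decision before the outcome data are analysed. The economic measures sections describe questionnaires at 6 and 9 months in the past tense, so some follow-up data already exist. The article does not say that any effect analysis has been done, and the amendment should confirm that none had been when the model was fixed.

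If a group-by-need-for-cognition term is wanted, label it optional and exploratory and keep it out of the primary model.

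The cost is one or two sentences, no new data and one degree of freedom. With 25% loss, about 257 × 0.75 = 193 participants remain, so the residual degrees of freedom at each time point fall from about 190 to 189.
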